**9.3.1.2 Cholestyramine**

Cholestyramine is a bile acid sequestrant and is used in the leflunomide elimination procedure. When given at a dose of 8 g three times a day for 24 hours to healthy volunteers, cholestyramine decreased the plasma levels of A77 1726 by 40% at 24 hours and by 49-65% in 48 hours.

As indicated in the package insert (submitted separately), use of cholestyramine is contraindicated in patients with complete biliary obstruction, hyperlipoproteinemia types III, IV, or V, or known hypersensitivity to bile acid sequestering resins.

The most common adverse reactions caused by cholestyramine are gastrointestinal including constipation, abdominal discomfort, nausea, flatulence, vomiting, diarrhea, heartburn, anorexia, and indigestion. Mild steatorrhea may also occur. Constipation is the most common complaint of cholestyramine users. Cholestyramine should be used with caution in patients with constipation at baseline, and routine use of a stool softener should be considered with long term use of cholestyramine. Complete intestinal obstruction has been reported in a couple of patients.

Other adverse effects of cholestyramine include rare reports of hematologic effects. Bleeding tendencies due to hypoprothrombinemia have been reported as well as one case of platelet gigantism.

Hyperchloremic acidosis has been reported to occur in small children and older adults receiving concomitant spironolactone therapy.

Elevated thyrotropin levels with a corresponding reduction in serum free thyroxine values occurred in a few hypothyroid patients who were receiving thyroid hormone and cholestyramine concurrently. It is unknown if the alteration in the thyroid function tests were due to a drug interaction or an alteration of thyroid function.

Cholestyramine may interfere with normal fat absorption and thus prevent absorption of fat soluble vitamins A, D, E, and K.

Sipping or holding the resin in the mouth for prolonged periods may lead to changes in the surface of the teeth resulting in discoloration, erosion of enamel or decay.

There is one reported case of urinary tract calculi associated with cholestyramine therapy.

Cholestyramine may interfere with drugs that undergo enterohepatic circulation. Concomitant drugs should be taken an hour before or 4-6 hours after taking cholestyramine. There are additive effects with cholestyramine and HMG-CoA reductase inhibitors and nicotinic acid. Cholestyramine may reduce of delay absorption of several medications (see Appendix B – Medications that Have Interactions with Cholestyramine)

**9.3.2 Other Risks**

Blood drawing has associated risks that include bruising, bleeding, and rarely fainting or infection. No more then 450 cc of blood will be drawn during a 6-week period in accordance with NIH guidelines.

This research study involves exposure to radiation from a chest x-ray, which is for research purposes only.  The amount of radiation involved in this procedure confers minimal risk and is necessary to obtain the research information desired. A chest X-ray involves exposure of 100 mrem to the skin of the chest and the calculated effective dose is 29 mrem. The amount of radiation exposure in this study is below the dose guideline established by the NIH Radiation Safety Committee for research subjects.  This guideline is an effective dose of 5 rem (or 5,000 mrem) received per year.

# 9.4 Compensation

There will be financial compensation of $640.00 for those who enroll and complete the entire study. Participants will also receive partial remuneration for the immediate costs associated with their study-related expenses like travel expenses, lodging, etc., as provided by the NIH.

In the event of an injury occurring as a result of participation in this research study, participants will be advised to seek immediate necessary medical care from their home physician. There is no provision for long term free medical care or for monetary compensation from any injury from the physicians conducting this study, from the National Institute of Allergy and Infectious Diseases (NIAID) or from the Clinical Center of the National Institutes of Health.

# 9.5 Consent/Assent Procedures

The protocol will be discussed verbally between the patient and one of the senior investigators at OP8 during which time the patient will have ample opportunity to discuss any questions. The patient will then be given the opportunity for discussion with one of the senior investigators. If protocol enrollment is then agreeable, the patient will sign the consent document and treatment will commence.

9.6 Confidentiality

All laboratory specimens, evaluation forms, reports, and other records that leave the site will be identified by coded number only in order to maintain subject confidentiality. All records will be kept locked. All computer entry and networking programs will be done with coded numbers only. Clinical information will not be released without written permission of the subject, except as necessary for monitoring by IRB, the FDA, and the NIAID.

**11.0 Appendices**

11.1 Appendix A - Medications that are metabolized by CYP 2C9 and contraindicated during treatment period

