**1.4 Leflunomide: metabolism, mechanism of action, and use in rheumatoid arthritis**

Leflunomide is an isoxazole immunomodulatory agent that was approved by the FDA in 1998 for the treatment of rheumatoid arthritis. Following oral administration, leflunomide is rapidly and almost completely converted to an open-ring metabolite A77 1726, also referred to as M1 (23). The specific site of metabolism is unknown but in vivo and in vitro studies suggest a role for both the GI wall and the liver in drug metabolism. No specific enzyme has been identified as the primary route of metabolism for leflunomide; however, hepatic cytosolic and microsomal cellular fractions have been identified as sites of drug metabolism. M1 has also been identified as an inhibitor of cytochrome P450 isoenzyme 2C9. The primary metabolite, M1, is eliminated by renal excretion as well as by direct biliary excretion and has a half-life of approximately 2 weeks. Because of the long half-life, a drug elimination procedure (cholestyramine 8 g three times daily for 11 days) is recommended to expedite the removal of drug from plasma in the case of unexpected pregnancy or adverse event while receiving leflunomide. Administration of cholestyramine reduces the half-life of leflunomide to one day, most likely by interfering with biliary recycling of M1.

The M1 metabolite is a malononitrilamide to which most of the immunomodulatory effects of leflunomide are attributed. At low therapeutically applicable doses, M1 reversibly inhibits dihydroorotate dehydrogenase (DHODH), the rate limiting step in the de novo synthesis of pyrimidines. This results in inhibition of orotate production and decreased de novo synthesis of rUMP. The diminished level of rUMP results in p53 activation and translocation into the nucleus. After activation of p53, the damaged T cell will arrest in late G1 and not enter the S phase of the cell cycle, required for cell replication (24). As a result, there is inhibition of T cell proliferation resulting in decreased immune response.

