**4.4.2 Treatment period (Day 1 through 28)**

Patients must have stopped taking contraindicated medications one week prior to Day 1 (see Appendix A - Medications Metabolized by CYP 2C9 and Contraindicated During Treatment Period). Day 1 through 28, patients will receive leflunomide 20 mg orally, once daily or placebo. If appropriate, a urine pregnancy test will be performed on Day 1 before delivery of study drug.

On Days 1 and 15 of study, patients will return for clinic visits (it will be sufficient if patients come within plus or minus 2 days of each study visit during the treatment period and within plus or minus 7 days during the post-treatment follow up period). At these visits their history will be reviewed and they will undergo a targeted physical exam to be driven by any signs or symptoms identified by the patient. The targeted physical exam will also include temperature, pulse, blood pressure, respiratory rate and examination of the heart, lungs and abdomen. Patients will have urine sent for pregnancy testing if appropriate and blood drawn for safety labs, HIV viral load, CD4+ and CD8+ T cell counts, expression of Ki67, expression of activation markers, memory/naïve phenotyping, expression of coreceptors (CCR5 and CXCR4), ELISA for IL-7, TNF level, lymphoproliferative responses, Annexin V staining and *ex vivo* BrdU. Additionally, blood will be drawn for measurement of the main metabolite of leflunomide, M1 or A77 1726. On Day 1, blood will be drawn for these labs prior to administration of medication so that these values will serve as baseline values.

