**4.4.3 Post-treatment follow up period (Day 29 through 64)**

On Day 29, the patient’s treatment arm will be unblinded. Patients who were receiving placebo will end study on Day 29. Patients who were receiving leflunomide will begin the drug elimination procedure: cholestyramine 8 grams orally three times a day for 11 days over the following 14 days. On Day 43, a serum A77 1726 level will be measured to assure elimination of the drug metabolite from the serum. Drug level should be less than 0.02 mg/L (or 0.02 ug/mL). If A77 1726 is less than 0.02 mg/L, the patient will end study on Day 64. If the level is above 0.02 mg/L, the 11 day cholestyramine elimination procedure will be repeated, and the study period will be extended as needed.

During the post-treatment follow up period, patients will come in for study visits on Days 29, 43 and 64. On these days, they will have their histories reviewed, urine will be sent for pregnancy testing when appropriate, and blood will be drawn for safety labs, HIV viral load, CD4+ and CD8+ T cell counts. On Days 29 and 43, blood will also be drawn for research studies of lymphocytes including expression of Ki67, expression of activation markers, memory/naïve phenotyping, expression of coreceptors (CCR5 and CXCR4), ELISA for IL-7, TNF level, lymphoproliferative responses, Annexin V staining and *ex vivo* BrdU as well as for measurement of A77 1726. On Days 29 and 43 they will undergo comprehensive physical exams and on Day 64 a targeted physical exam.

Table 1. Procedures

|  | Scr | H&P | D11 | D15 | D29 | D432 | D642 |
| --- | --- | --- | --- | --- | --- | --- | --- |
| Screening consent | X |  |  |  |  |  |  |
| Standard consent |  | X |  |  |  |  |  |
| History | X | X | X | X | X | X | X |
| Comprehensive physical exam |  | X |  |  | X | X |  |
| Targeted physical exam |  |  | X | X |  |  | X |
| EKG and CXR | X |  |  |  |  |  |  |
| HLA testing | X |  |  |  |  |  |  |
| Safety labs3 | X | X | X | X | X | X | X |
| Urine pregnancy test4 | X | X | X | X | X | X | X |
| HIV ELISA5 | X |  |  |  |  |  |  |
| Hep B, C serology6 | X |  |  |  |  |  |  |
| Lipid panel | X |  |  |  |  |  |  |
| HIV viral load | X | X | X | X | X | X | X |
| Flow cytometry | X7 | X7 | X8 | X8 | X8 | X8 | X7 |
| Additional studies9 |  |  | X | X | X | X |  |
| A77 1726 level |  |  | X | X | X | X |  |

1. On Day 1, blood will be drawn prior to administration of study drug

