# 5.2 Exclusion Criteria

1. Current treatment with antiretrovirals or use of antiretrovirals within 12 weeks of screening
2. Intention to start antiretroviral regimen within 64 day study period
3. Previous treatment with leflunomide
4. Previous treatment with IL-2
5. Treatment with immunomodulatory agents (including hydroxyurea, mycophenolate, cyclosporine, rapamycin, anti-HIV vaccines, interleukins other than IL-2, interferons) within 60 days of study
6. Treatment with systemic corticosteroids within 30 days of study
7. Inability or unwillingness to discontinue drugs (except NSAIDs) that are metabolized by P450 2C9 isoenzyme (see Appendix A - Medications Metabolized by CYP 2C9 and Contraindicated During Treatment Period).
8. Inability or unwillingness to discontinue hepatotoxic drugs (eg. isoniazid, rifampin, HMG CoA reductase inhibitors)
9. Inability or unwillingness to discontinue drugs that interact with cholestyramine (eg. have diminished absorption with cholestyramine) (see Appendix B – Medications that Have Interactions with Cholestyramine)
10. Current use of or known intolerance of cholestyramine or bile acid sequestering resins
11. History of familial hyperlipoproteinemia type III, IV or V
12. Active bacterial infection within 4 weeks of screening
13. History of AIDS-defining illness (category C) (see Appendix C - CDC AIDS Classification Criteria)
14. Hepatitis B or C infection
15. Acute or chronic liver disease from any cause (eg. alcoholic hepatitis or alcohol induced cirrhosis, autoimmune hepatitis, primary biliary cirrhosis, sclerosing cholangitis, Wilson’s disease, hemochromatosis) which the investigator feels would compromise the subject’s safety
16. History of biliary obstruction
17. Current alcohol abuse or unwillingness to abstain from alcohol use for study period
18. History of hypertension that is not controlled (<140/80 mm/Hg) on a single antihypertensive agent
19. Abnormal laboratory findings: hemoglobin <10 g/dL; ANC <1000/mm3; platelets <100,000/mm3; creatinine above the upper limit of normal; ALT or alkaline phosphatase >1.25 times the upper limit of normal; AST >1.25 times the upper limit of normal* direct bilirubin >1.5 times the upper limit of normal; total bilirubin >2 times the upper limit of normal lipase > 1.5 times the upper limit of normal; PT >1.1 times the upper limit of normal; PTT>1.5 times the upper limit of normal.

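### The CYP 2C9 drug restriction is tied to Days 1 to 28, so ten of the 14 listed drugs have no stated rule while M1 is being eliminated: a minor safety gap with a cheap wording fix

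*Protocol*

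**What the plan says.** **When the restriction applies.** Appendix A carries the title "Medications that are metabolized by CYP 2C9 and contraindicated during treatment period". Section 4.4.2, whose heading defines the treatment period as Day 1 through 28, fixes the start ("Patients must have stopped taking contraindicated medications one week prior to Day 1") and gives no date for resuming. Exclusion 7 has no time limit in its own sentence, but it cites the appendix by the same time-limited title.

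**Why there is a restriction.** Section 1.4 states that "M1 has also been identified as an inhibitor of cytochrome P450 isoenzyme 2C9" and gives M1 a half-life of about two weeks.

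**What happens from Day 29.** Under section 4.4.3 the arm is unblinded, placebo patients leave the study, and leflunomide patients begin "cholestyramine 8 grams orally three times a day for 11 days over the following 14 days". Clearance is checked two weeks later: "On Day 43, a serum A77 1726 level will be measured to assure elimination of the drug metabolite from the serum". That section has no rule on concomitant drugs. Section 1.4 adds: "Administration of cholestyramine reduces the half-life of leflunomide to one day".

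**Other rules that touch the listed drugs.** Exclusion 9 bars patients for "Inability or unwillingness to discontinue drugs that interact with cholestyramine", which are listed in Appendix B. Section 6.3 makes starting an Appendix A or B drug, and refusing to stop it, a reason to stop study drug.

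**The concern.** The restriction exists because M1 inhibits the enzyme that metabolises these drugs. Its end should therefore follow the presence of M1, not the last tablet. With a two-week half-life the two are far apart. As worded, the restriction is in force on Day 1, when M1 is only starting to build up, and its stated period ends after Day 28, when M1 is close to its highest level in the study.

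A patient who paused one of these drugs to enrol could resume it on Day 29, or after stopping early, without breaking any written rule, while a substantial amount of inhibitor is still present. Such a patient is plausible. Exclusion 18 admits hypertension controlled on one agent, and losartan and irbesartan are both on the Appendix A list. What is at stake is avoidable drug interaction exposure in a few people, not the trial's efficacy conclusion.

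**Working it through.** The protocol gives no figure of its own for this exposure, so there is none to reproduce. Two checks were made.

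**1. Which drugs are left without a rule.**
- Appendix A names 14 drugs.
- Four are also in Appendix B: glipizide, fluvastatin, phenytoin and warfarin. Exclusion 9 is read as keeping these off while cholestyramine is given, since that is its purpose, although it states no window.
- The other 14 − 4 = 10 are not in Appendix B: tolbutamide, glyburide, losartan, irbesartan, amitriptyline, celecoxib, fluoxetine, rosiglitazone, tamoxifen and torsemide.
- The section 6.3 item does not close the gap. Its consequences are stopping study drug, unblinding and elimination, and all three have already happened by Day 29.

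**2. How much M1 is present.** Inputs:
- half-life 14 days without cholestyramine (section 1.4);
- 28 equal daily doses with no loading dose (section 4.4.2);
- half-life on cholestyramine of 1.0 day (section 1.4), or the value implied by the 40% fall at 24 hours in section 9.3.1.2: ln 2 / −ln 0.60 = 1.36 days.

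The 48-hour falls of 49-65% in section 9.3.1.2 are not used for the main range, because cholestyramine was given for only 24 hours there. A one-compartment model is assumed.

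- After the Day 28 dose, relative to steady state: 1 − 2^(−28/14) = 0.75.
- After the first dose, relative to that peak: (1 − 2^(−1/14)) / 0.75 = 0.048 / 0.75, about 6%.
- Start of Day 29, before cholestyramine, relative to peak: 2^(−1/14) = 0.952, about 95%.
- Time to 10% of the Day 29 level on uninterrupted cholestyramine: h × log2(10), with h the half-life. This gives 1.0 × 3.32 = 3.3 days and 1.36 × 3.32 = 4.5 days.
- With d days before cholestyramine starts: d + h × log2(2^(−d/14) / 0.10). If all three spare days in the 14-day window came first (d = 3, 86% remaining), this gives 6.1 to 7.2 days.

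**Level at the end of the 11-day course, relative to peak:** 0.952 × 2^(−11/h).
- h = 1.0: 0.05%.
- h = 1.36: 0.35%.
- h = 2.06, the slowest value implied by the 48-hour data (2 × ln 2 / −ln 0.51): 2.4%.

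Spare days within the 14-day window only lower these figures, so in this model completing the course ensures the fall wherever the gaps lie.

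**The case against.** **Nothing permits a restart on Day 29.** This is correct. A reader might infer from the appendix title that the protocol authorises these drugs from Day 29, but it does not say so. The operative sentence of exclusion 7 is open-ended, and one can object that exclusion 9 is read here as reaching past Day 28 while exclusion 7 is not. The difference is that exclusion 7 points to a list whose title carries an end point, and exclusion 9 does not. If exclusion 9 were read as an entry check only, more drugs would be uncovered, not fewer.

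**Day 29 already applies the protocol's remedy.** Dosing has ended, the arm is known, elimination starts, and there is a full examination with safety laboratory tests. This limits the risk considerably. It does not tell the clinician when a paused drug may resume.

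**M1 is near its peak only briefly.** This is also correct. A reader might infer near-peak exposure until the Day 43 check, but on cholestyramine M1 falls to 50-60% of its Day 29 level within one day.

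**Longer windows need stacked assumptions.** The visit window ("within plus or minus 7 days during the post-treatment follow up period") allows one to construct 9.8 to 10.8 days if the Day 29 visit is a week late and cholestyramine waits for it, and 12.6 to 13.5 days if the three spare days also come first. Those cases need the patient to resume a listed drug before a late visit, while still blinded, or cholestyramine to be postponed although section 4.4.3 has patients begin it at Day 29. After the main safety stops in section 6.3, elimination starts at once. The longer figures should not be taken as typical.

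**No harm is shown.** The documents report no clinical consequence for any of the ten drugs and give no M1 level at which CYP 2C9 inhibition stops mattering. NSAIDs, also CYP 2C9 substrates, are allowed throughout on the strength of cited experience. The severity is therefore minor. The protocol offers no comparable support for the ten drugs, however, and itself chose to contraindicate them.

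**Conclusion.** The point holds as a minor safety matter and a cheap improvement. The protocol ties the restriction to Days 1 to 28, states no rule afterwards for ten of the 14 drugs, and by its own facts leaves M1 at about 95% of peak at the start of Day 29. The best-supported exposure window is about 3.3 to 4.5 days to 10% of the Day 29 level, somewhat longer if cholestyramine is delayed or interrupted.

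At most 12 leflunomide patients are concerned (section 4.3), and the documents do not say how many would have such a drug to resume. The primary endpoint and the sample size are unaffected.

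The conclusion rests on the half-lives in sections 1.4 and 9.3.1.2, a one-compartment model, and reading exclusion 9 as covering the cholestyramine period. The 10% level is only a reference point, not a safety threshold.

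**What to change.** In the Appendix A title, and where section 4.4.2 and exclusion 7 cite it, replace the reference to the treatment period with: during the treatment period and, for leflunomide recipients (including those who stop early), until the 11-day cholestyramine elimination course is complete. State that placebo patients are released at unblinding.

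Completion of the course is preferable to the 0.02 mg/L result as the end point. That level is the protocol's elimination criterion, and the documents do not link it to CYP 2C9 inhibition. Course completion matches the period over which Appendix B drugs are taken to be restricted, and M1 is then under 3% of peak even on the slowest half-life implied by the documents.

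The cost is a wording amendment with matching site and consent instructions, and no added visit or test. The downside is up to about two more weeks (Day 29 to Day 43) on substitute treatment for the few patients who paused a listed drug.

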## Oral hypoglycemic agents

Tolbutamide

Glipizide

Glyburide

## Angiotensin II blockers

Losartan

Irbesartan

## Other

Amitriptyline

Celecoxib

Fluoxetine

Fluvastatin

Phenytoin

Rosiglitazone

Tamoxifen

Torsemide

Warfarin

Note: NSAIDs (eg. diclofenac, ibuprofen, meloxicam, naproxen, piroxicam, suprofen) although metabolized by CYP 2C9, have been used safely in clinical trials in combination with leflunomide (28, 29, 34). Additionally a multidisciplinary panel of experts in rheumatoid arthritis has agreed that NSAIDs can be used safely in combination with leflunomide (35). Therefore, the use of NSAIDs, at FDA-approved doses, is allowed during this study.

**11.2 Appendix B – Medications that Have Interactions with Cholestyramine**

amiodarone

anisindione

aspirin

bezafibrate

carbamazepine

cephalexin

cerivastatin

chloroquine

chlorothiazide

cholecalciferol

clopamide

cyclosporine

diclofenac

dicumarol

digitoxin

digoxin

doxepin

doxercalciferol

entacapone

estrogens

fenofibrate

fluvastatin

furosemide

glipizide

hydrochlorothiazide

hydrocortisone

iopanoic acid

iron

levothyroxine

liothyronine

lorazepam

meloxicam

methacycline

methotrexate

metronidazole

mycophenolate mofetil

niacin

penicillin G

phenobarbital

phenprocoumon

phenylbutazone

phenytoin

piroxicam

pravastatin

progestins

raloxifene

sulindac

tenoxicam

tetracycline

thyroglobulin

troglitazone

tyropanoate sodium

ursodiol

valproic acid

warfarin

**11.3 Appendix C** **- CDC 1993 Revised Classification System for HIV Infection and Expanded Surveillance Case Definition for AIDS Among Adolescents and Adults**

